## Background

### Body image in childhood

Body image – the way people think, feel, and behave in relation to their body – encompasses two distinct constructs; negative body image (i.e., body dissatisfaction) and positive body image (i.e., an overarching love, respect, appreciation for, and acceptance of the body and what it can do [1]). Traditionally, body dissatisfaction has been viewed as a problem that develops during adolescence; however, such concerns may develop much earlier than this [2, 3]. Typically, very young children (e.g., ages 3–5 years) express positive feelings towards their bodies [4], with some beginning to report body dissatisfaction during early years of schooling [5]. Negative attitudes towards other people’s bodies, particularly weight bias, can emerge as early as three years ( [6]). By age five years, many children have internalised appearance ideals [7] and by age six, a large proportion of children (up to 70%) report dissatisfaction with specific body parts, weight and/or shape [8, 9], and a desire to be thinner or more muscular for girls and boys respectively [5, 10]. Body dissatisfaction becomes problematic when high value or investment is placed upon appearance [11]. Appearance investment often peaks as children emerge into pre-adolescence, a period when body dissatisfaction can become entrenched [12]. Together, this highlights a small but unique window of opportunity to shape and nurture the development of positive body image among younger children to harness their existing positive attitudes and potentially prevent the future onset of body dissatisfaction.

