### Statistical power and sample size

A proposed sample of 440 children aged 4–6 years and a corresponding parent will be recruited for this study. The study has been powered for immediate post intervention effects to be assessed using analysis of covariance with the commensurate baseline measure as the covariate. Caution has been exercised for assumed for effect size due to a universal non-clinical population undergoing a micro-intervention. This is offset by an assumed medium to large pre- post- correlation due to the short time interval between measures and the high degree of internal validity at data collection. For a two-sided test (alpha = 0.05), a sample size of *n* = 103 per arm will have 90% power for an assumed standardised effect of Cohen’s delta = 0.3, with pre-post-correlation of 0.75. A sample size of *n* = 92 per arm will have 80% power for a standardised effect of Cohen’s delta = 0.25 with pre- post- correlation of 0.8. The aim is to sample for *n* = 105 per arm (90% power, *r* = 0.75, *d* = 0.3). To achieve sample size, the target recruitment will be inflated to *n* = 110 per arm to compensate for any missing data.

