### Statistical analyses

At trial completion, the data will be entered into SPSS, cleaned, screened and the T2 acceptability data separated out for concealment purposes. The concealed dataset will be delivered to the statisticians to conduct analyses.

The primary analysis will be on an Intention-to-Treat (ITT) basis inclusive of all randomised participants who provide some outcome data either immediate post-intervention (T2) or at follow-up (T3). Conclusions will be drawn from the ITT analysis set. In addition, a supplementary per-protocol analysis set, excluding any protocol deviations, will be undertaken. Prior to inferential analysis there will be a validity and verification assessment for data veracity. The primary outcome measure is body appreciation with endpoint being body appreciation immediate post intervention (T2). The primary analysis will be an analysis of covariance comprising randomised arm and body appreciation at T1 as a covariate. This model will include a baseline by covariate interaction term if necessary for model validity. Underpinning assumptions will be assessed for model validity and remedial action taken if required (e.g., robust homoscedasticity corrected analyses or bootstrap approaches as deemed necessary to ensure valid statistical conclusions). If the data is highly discrete to the extent of potentially compromising statistical conclusions, then the linear link function will be replaced by a more appropriate link function (e.g., ordinal logistic regression or negative binomial regression). If the baseline by covariate interaction term is deemed important then a follow-up Johnson-Neyman analysis of covariance will be used. These analysis of covariance models will compare (i) music intervention and music control using the data from the two appropriate arms, and (ii) 15-minute episode intervention and 15-minute episode control using the data from the two appropriate arms. Effect sizes, 95% Confidence Intervals and standardised effects will be reported as appropriate.

The above analyses will be extended to assess any moderating effects by gender, and any moderating effects by year group.

Secondary exploratory analysis will compare the 15-minute intervention and music intervention using the data from the two appropriate arms using the same methodological process.

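### The primary ANCOVA may gain a misnamed interaction term if the data suggest it, and the plan does not say which estimate then decides the primary hypothesis

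*Protocol article*

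**What the plan says.** Under Statistical analyses, the protocol article sets one primary outcome (body appreciation), one endpoint (T2) and one default model: ANCOVA with randomised arm and T1 body appreciation. It is fitted separately to the music-video pair and the 15-minute-episode pair.

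Two conditional steps follow. The first changes the model itself: "This model will include a baseline by covariate interaction term if necessary for model validity". The second adds to it: "If the baseline by covariate interaction term is deemed important then a follow-up Johnson-Neyman analysis of covariance will be used". Neither step has a stated trigger, and the section does not say which estimate answers the primary question once the interaction is in the model. The same plan is carried over to functionality appreciation and weight bias, and to the exploratory comparison of the two interventions.

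The section also allows variance-robust or bootstrap analysis, and a different link function if the data are highly discrete. The statisticians receive a concealed dataset.

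The sample size section powers the trial for immediate effects "to be assessed using analysis of covariance with the commensurate baseline measure as the covariate", with no interaction term.

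**The concern.** There are three linked problems.

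- **The term is wrong as written.** T1 body appreciation is both the baseline and the only covariate, so a baseline-by-covariate interaction is the baseline with itself. Arm by T1 score must be intended. The slip occurs twice.
- **The reason given does not hold.** In a randomised comparison T1 score is independent of arm. The main-effect arm coefficient therefore estimates the average difference between arms even when the T1 slopes differ. Unequal slopes matter for describing who benefits, not for the validity of the average effect.
- **The deciding estimate is left open after the switch.** At least three quantities could be read: the arm effect at mean T1, the arm coefficient as printed, or a region of T1 values where the arms differ. Their error rates are not the same.

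At stake is whether the 5% level applies to the primary result if the interaction is added. So is whether the reader gets one effect estimate per pair or a range of baseline values.

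**Working it through.** **1. The plan's own sample size.** Inputs come from Statistical power and sample size: "For a two-sided test (alpha = 0.05), a sample size of" 103 "per arm will have 90% power for an assumed standardised effect of Cohen’s delta = 0.3, with pre-post-correlation of 0.75". For ANCOVA with baseline correlation r, the size per arm is n = 2(1 − r²)(z₀.₉₇₅ + z_power)² / d².

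- d = 0.3, r = 0.75, 90% power: 2 × 0.4375 × (1.960 + 1.282)² / 0.09 ≈ 102.2, so 103. Stated: 103.
- The second scenario is stated as 92 "per arm will have 80% power for a standardised effect of Cohen’s delta = 0.25 with pre- post- correlation of 0.8": 2 × 0.36 × (1.960 + 0.842)² / 0.0625 ≈ 90.4, so 91. The one-unit difference is immaterial.

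The figures reproduce, and they belong to the model without interaction. "The aim is to sample for *n* = 105 per arm"; at 105, power is 90.8% (normal) or 90.5% (noncentral t).

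**2. What the coefficients mean.** Write Y = a + b·arm + c·T1 + e·arm·T1. The effect at a given T1 is b + e·T1.

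- If T1 is uncentred, b is the effect at T1 = 0. The score is the mean of two items scored 1 to 4, so 0 is off the scale.
- If T1 is mean-centred, b is the effect at the average baseline, which is the quantity the default ANCOVA targets.

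**3. False-positive rate by reading.** This is a null simulation of one two-arm comparison with 105 per arm, using ordinary least-squares standard errors (40,000 replicates for the first row, 20,000 for the others). The switch is taken to occur at interaction p < 0.05 except in row 2. Triggers, success rules and ceiling shares are assumptions, since the document states none.

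| Null data | Switch fires | Main-effect ANCOVA only | After switch: effect at mean T1 | After switch: uncentred coefficient | After switch: any Johnson-Neyman region |
|---|---|---|---|---|---|
| Normal, r = 0.75 | 5.0% | 5.0% | 5.0% | 8.3% | 9.5% |
| Normal, trigger p < 0.10 | 9.7% | 5.3% | 5.3% | 9.2% | 11.6% |
| Two 4-point items, 35% of answers in top category | 2.7% | 4.9% | 4.9% | 6.9% | 6.9% |
| Two 4-point items, 70% of answers in top category | 15.4% | 4.6% | 4.9% | 17.6% | 17.4% |

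Row 1 can be checked by hand. When the switch fires, some region is nearly always significant (4.78% of all trials, against a firing rate of 5.0%). Otherwise the ANCOVA rejects about 5% of the time: 4.78% + 0.95 × 4.98% ≈ 9.5%. The upper bound for two independent 5% chances is 1 − 0.95² = 9.75%.

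**4. Effect of the variance correction the plan allows.** A further null simulation used 6,000 replicates, about 48% of children at the T1 maximum and an assumed latent pre-post correlation of 0.75. With HC3 standard errors the interaction test rejects 4.7% of the time instead of 9.1%. The any-region rule gives 8.4% instead of 12.6%. Reading the effect at mean T1 gives 5.1%.

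**5. When the intervention works.** With an assumed latent shift of 0.35 SD, the interaction test fired in 13%, 24% and 36% of simulated trials with 29%, 44% and 60% of children at the T1 maximum. Children at the maximum cannot improve, so slopes diverge.

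**The case against.** A reader might infer that the trial has no single primary test. The text does not support that. It names one default ANCOVA, powers that model, and calls Johnson-Neyman a follow-up. It nowhere says that a significant region would count as primary success.

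A reader might also infer that the procedure necessarily raises the error rate above 5%. It does not. Reading the arm effect at mean T1 after the switch keeps the rate near 5%, and the document does not exclude that reading. The largest rates also ignore the variance correction that the same section permits.

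Nor is it shown that the switch would fire often. Under the null it fired in 2.7% to 15.4% of the tabulated runs, and the top figure needs a strong ceiling. The ceiling is itself uncertain. The background says "Typically, very young children (e.g., ages 3–5 years) express positive feelings towards their bodies", but it also reports dissatisfaction in up to 70% by age six, and the trial enrols ages 4 to 6. The pilot checked this outcome for ceiling effects, and one item was chosen partly because its answers varied.

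Finally, centring and trigger thresholds are details that an analysis plan may settle, and the statisticians work on concealed data.

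These points remove the categorical claims and lower the size. They leave the following standing: the term is misnamed, the validity rationale is mistaken, and the article itself writes a data-dependent change into the primary model without fixing the deciding estimate. Concealment limits choice by direction of result, but the inflation in the table comes from a mechanical pre-test and occurs with blinded analysts too.

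**Conclusion.** The point holds as a defect in how the primary analysis is fixed, and it should be corrected. The interaction is misnamed and is not needed for validity, and once it is added nothing says what decides the primary hypothesis.

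The size depends on the reading:

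- About 5% per comparison if the arm effect at mean T1 is kept.
- About 8 to 10% if any Johnson-Neyman region or the uncentred coefficient were taken as the result (6.9% in the mildest setting tried).
- Roughly 15% with a strong ceiling and uncorrected standard errors (12.6% to 17.6% in the runs shown).

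The two higher ranges assume a trigger of p < 0.05, a success rule the document does not state, and ceiling shares it does not report. They show what the wording permits, not a property of the trial.

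**What to change.** In Statistical analyses:

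- State that, for each intervention-control pair, the deciding test is the arm effect from the main-effect ANCOVA of T2 body appreciation on arm and T1 score, with heteroscedasticity-robust standard errors, whatever the interaction shows. The model can also include gender and year group, which already stratify the randomisation.
- Rename the interaction as arm by mean-centred T1 body appreciation, in both places.
- Label that interaction and any Johnson-Neyman region as supplementary description.

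The same wording then carries over to the secondary outcomes. With this rule the simulated error is about 5% per comparison and power stays at about 90% with 103 to 105 per arm. The cost is two or three sentences, settled before the concealed dataset is analysed, with no change to data collection or sample size. The separate provision for changing the link function is not resolved by this edit.

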#### Pilot study

A small internal pilot study was conducted at the end of 2023 for the purpose of trialling the research design and protocols. A stop-go protocol was implemented, and progression criteria was based on; (1) feasibility assessment such as participant recruitment, retention, and evidence of ceiling/floor effects on the primary outcome measure and (2) harm assessment including evidence of child distress due to the content / research process reported by children, parents, or moderators. Criteria was rated for each parameter with a traffic light system of green, amber, and red as seen in Table 1.

**Table 1 Tab1:** Stop-go progression criteria

Criteria			Green	Amber	Red
1. ***Feasibility assessment***					
Participant recruitment	*How many participants showed up at T1?*		**More than 80%** Continue to main trial	**Between 60–80%** Consult research team and review recruitment plans	**Less than 60%** Pilot study may need to be extended
Participant retention at T3	*How many participants showed up at T3?*		**More than 80%** Continue to main trial	**Between 50–80%** Consult research team and discuss strategies to increase retention	**Less than 50%** The main trial will need to reconsider the inclusion of T3
Ceiling and/or floor effects on the primary outcome	*Is there evidence of ceiling or floor effects at T1 on the primary outcome measure*,* child body appreciation?*		**No** Continue to main trial	**Partial** Consult research team and discuss potential measure amendments	**Yes** The main trial will need to potentially reconsider the response scale for the primary outcome
2. ***Harm assessment***					
Child distress	*Were any of the children visibility distressed?*,* did any of the children tell the moderators anything concerning?*,* did any parent withdraw their child during the pilot due to the content or research process?*		**None** Continue to main trial	**Between 1–10%** Review feedback from moderators and parents, consult with the research team	**More than 10%** All cases to be qualitatively investigated and the team to consider the safety of the trial

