The above analysis plan for body appreciation will be repeated for the secondary outcome measures of functionality appreciation and weight bias. Secondary research questions at T3 will be examined using the same analysis of covariance methods controlling for baseline (T1).

The aim is to have ITT data on *N* = 420 participants. This will be achieved through a target recruitment of *N* = 440 cognisant that some potential participants might be unable to partake in the research due to external mitigating reasons. If the size of the ITT analysis set is N > = 380 then the data will be analysed as given. If the size of the ITT analysis set due to missing data is between 260 and 380 then a full missing values analysis will be undertaken, and appropriate sensitivity analyses performed. If the size of the ITT analysis set due to missing data is less than 260 then results will be given descriptively.

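### Missing-data work is triggered by a pooled four-arm count of children with T2 or T3 data, so T3 loss after T2 never triggers it, and a total below 260 makes every result descriptive

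*Protocol article*

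**What the plan says.** All of the following is in the Protocol article. The Statistical analyses section defines the ITT set as "inclusive of all randomised participants who provide some outcome data either immediate post-intervention (T2) or at follow-up (T3"). The primary endpoint is body appreciation at T2. It is analysed by ANCOVA on T1, separately for the music pair and the episode pair, each using two of the four arms. The T3 questions use the same ANCOVA method.

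The same section then sets three bands on the size of that set:
- At the top: "If the size of the ITT analysis set is N > = 380 then the data will be analysed as given".
- From 260 to 380: a full missing-values analysis and sensitivity analyses.
- At the bottom: "If the size of the ITT analysis set due to missing data is less than 260 then results will be given descriptively".

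No band is stated per arm, per comparison, per outcome or per time point. Under Procedure, T1 and T2 fall in one session and T3 follows seven to ten days later. In Table 1 (Pilot study), T3 retention of 50 to 80% is rated amber, with the action "Consult research team and discuss strategies to increase retention".

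**The concern.** A trigger for missing-data work should respond to the data missing from the analysis concerned. This one responds to a different quantity, in three ways.

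- **Time point.** Either T2 or T3 data qualifies a child, so data missing at one visit are masked by data at the other. The main case is a child seen at T2 who does not return.
- **Outcome.** Any outcome data qualify. A child with no usable T2 body appreciation score, but with another T2 measure or T3 data, counts toward 380 yet cannot enter the primary ANCOVA. The Discussion itself expects some unusable responses and refusals.
- **Arms.** The count runs over four arms and each comparison uses two, so heavy loss in one arm can be offset by completeness elsewhere.

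T3 results could therefore be reported from complete cases after substantial loss, with no sensitivity analysis required. That loss comes after families have seen their assigned media, so it can be related to arm. At the other end, the floor of 260 decides how the primary result is presented by a pooled count, whatever the state of the comparison in question.

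**Working it through.** **Inputs.** From Statistical power and sample size: two-sided alpha 0.05; "103 per arm will have 90% power" at "delta = 0.3, with pre-post-correlation of 0.75"; "92 per arm will have 80% power" at d = 0.25 and r = 0.8; recruitment of 110 per arm, 440 in total. From Statistical analyses: the thresholds 380 and 260. From Pilot study: 80 enrolled, 63 attended, 61 usable.

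**1. The plan's own sample sizes.** For ANCOVA, n per arm = 2(z₁₋α/2 + z₁₋β)²(1 − r²)/d².
- d = 0.3, r = 0.75, 90% power: 2 × (1.960 + 1.282)² × 0.4375/0.09 ≈ 102.2, so 103. This matches.
- d = 0.25, r = 0.8, 80% power: 2 × (1.960 + 0.842)² × 0.36/0.0625 ≈ 90.4, so 91. The plan says 92, and the noncentral t gives 80.3% at 92. This is consistent.

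Power below uses the noncentral t with df = n₁ + n₂ − 3 and noncentrality d/[√(1 − r²) × √(1/n₁ + 1/n₂)], at d = 0.3 and r = 0.75. The plan gives no d or r for T3, so using these values there is an assumption.

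**2. What the thresholds mean if loss is even.**
- 380/4 = 95 per arm; 60/440 = 13.6% missing; power 87.5%.
- 260/4 = 65 per arm; 180/440 = 40.9% missing; power 72.8%.
- For comparison, 110 per arm gives 91.8%.

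**3. Loss at T3.** Suppose all 440 give T2 data. The counted set is then 440 whatever happens at T3. The two ends of the pilot's amber band serve as illustrations:

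| T3 retention | T3 analysed | Per arm | Power | Counted set | Rule applied |
|---|---|---|---|---|---|
| 80% | 352 | 88 | 84.9% | 440 | top band |
| 50% | 220 | 55 | 65.4% | 440 | top band |

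Counted at T3, 352 would fall in the middle band and 220 below the floor. As written, neither triggers anything.

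**4. Loss in one arm.** With the other three arms complete at 110, 330 + 50 = 380, so the fourth arm can lose 60 of 110 (54.5%) and stay in the top band. The comparison is then 110 v 50, with power 75.3%. A loss of 61 gives 379 and does trigger the missing-values analysis. Exactly 380 can be read into both the top and the middle band; on the stricter reading the largest loss without a trigger is 59 (53.6%). Starting from 105 per arm, 420 − 380 = 40 can be lost from one arm (38.1%), and the 41st loss triggers.

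**5. The floor.** A total of 110 + 110 + 39 = 259 leaves one comparison intact with 91.8% power, yet it falls under the descriptive-only rule. With even loss, 65 v 64 has 72.4% power.

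**6. When the rule does work.** Under Recruitment, randomisation comes before attendance, so a child who never attends leaves the set. At the pilot's rates, 440 × 63/80 = 346.5 attend and 440 × 61/80 = 335.5 are usable. Both lie in the middle band, so the missing-values and sensitivity analyses would run.

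**The case against.** The case for leaving the rule alone has real substance.

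- **The primary endpoint is largely protected.** T1 and T2 share a visit, so nearly every attender should have T2 data, and non-attendance does reduce the set. At pilot attendance the middle band applies. This stands, and it limits the consequence for T2. The plan gives no number for children who lack a usable T2 primary score but have other data.
- **The T3 questions are exploratory.** The Aims section says so, and the trial is powered for T2. This stands.
- **Heavy T3 loss is assumed.** The amber band is a pilot progression criterion, not a tolerance for the main trial. No T3 retention figure is reported, and the £130 incentive follows the T3 interview. This stands as a comment on likelihood. It does not alter how the rule behaves if loss occurs.
- **Completeness is checked in any case.** Data management promises screening for completeness, and tables of missingness are normally left to an SAP. That is fair, but a promise to screen does not override an explicit instruction on when missing-values and sensitivity analyses are run.
- **A floor is a cautious choice.** Below 260, more than 40.9% of 440 are missing, and retained power says nothing about bias. This is partly right. The weakness is that the floor is pooled and can catch an intact comparison.

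A reader might go further and infer that loss in one arm can never trigger the rule. The arithmetic contradicts that: the 61st loss from 110 does. A reader might also infer that all estimates and intervals disappear below 260. The plan says only that results will be descriptive, and elsewhere it promises effect sizes and 95% CIs, so the wording is unclear on this and does not exclude them.

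**Conclusion.** The point holds in a limited form. It concerns a rule that the article states, not something left out. T3 loss among children with T2 data cannot trigger missing-data work at any level: at 50% retention, 220 children would be analysed against a counted set of 440. Children missing the primary T2 score can be counted as present. More than half of one arm can be lost without a trigger if the other arms are complete. The floor of 260 can reduce a fully intact comparison to description.

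The effect is greatest for the exploratory T3 questions and smaller for the T2 primary result. The counts follow directly from the plan's definitions. The retention levels and loss patterns are illustrations, and the power figures rest on the plan's d = 0.3 and r = 0.75, carried over to T3 by assumption. The documents do not support saying that the rule is inert, or that the T2 ANCOVA itself is invalid.

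**What to change.** Reword the three bands before the analysis is seen:

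1. Apply the rule to the number actually analysed for each outcome, time point and two-arm comparison, and show missingness by arm.
2. Run the planned missing-values and sensitivity analyses when a comparison falls below its proportional threshold, for example 190 of 220 for two arms (380/2), or when missingness differs between its arms. The second condition is needed because one arm could still lose 30 of 110 and leave 190. State in advance what difference counts, and which band the boundary value belongs to.
3. Replace the below-260 rule with the planned estimate and 95% CI at any N, together with a caution on interpretation when loss is heavy.

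The T2 ANCOVA can stay. A longitudinal likelihood model using T1, T2 and T3 could be added as an optional sensitivity analysis, but nothing in the plan requires it. The cost is wording and modest extra analysis, with no new data.
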